**Methods/Design:**

The IMPROVing Evidence-based treatment Gaps and outcomes in community-Acquired Pneumonia (IMPROVE-GAP) trial is a pragmatic, investigator-initiated, stepped-wedge randomised trial. Patients hospitalised under a general internal medicine unit who meet a standard case definition for community-acquired pneumonia will be included. Eight general internal medicine units at two Australian hospitals in a single health service will be randomised using concealed allocation to: (i) usual medical, nursing and allied health care delivered according to existing organisational practice or (ii) care supported by a dedicated “community-acquired pneumonia service”: a multidisciplinary team deploying algorithm-based implementation of a bundle of the four evidence-based interventions. The primary outcome measure will be length of hospital stay. Secondary outcome measures include inpatient mortality, 30 and 90 day readmission rates and mortality and health-service utilisation costs. Protocol adherence will be measured and reported, and serious adverse events (rates of hyperglycaemia requiring new insulin; falls during mobilisation) will be collected and reported.

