Item 11. How well (planned): If intervention adherence or fidelity was assessed, describe how and by whom; if any strategies were used to maintain or improve fidelity, describe them	Patient proportions receiving: i) Corticosteroids ii) Pre-defined intravenous antibiotic stopping rules iii) Early mobilisation iv) Malnutrition Screening Tool application and appropriate nutrition therapy Aim for relevant proportions to exceed 70% for interventions (i) and (ii), and 85% for (iii) and (iv). Protocol adherence rates will be available to the project coordinator throughout the study, allowing high protocol non-compliance rates to be addressed in a timely fashion. Fidelity will be maximised by the daily interaction with community-acquired pneumonia team which promotes and monitors protocol adherence	Patient proportions receiving: i) Corticosteroids ii) Pre-defined intravenous antibiotic stopping rules iii) Early mobilisation iv) Malnutrition Screening Tool application and appropriate nutrition therapy. Anticipate existing data on proportions to be maintained
Item 12: How well (actual): If intervention adherence or fidelity was assessed, describe the extent to which the intervention was delivered as planned	Not applicable in protocol	Not applicable in protocol

The trial intervention is a 7 days/week evidence-based model of service (community-acquired pneumonia service) that comprises a multidisciplinary physiotherapist-led team (including medical, dietetics collaboration) that will conduct daily rounds of all patients managed by general internal medicine units assigned to the intervention.

The community-acquired pneumonia service will provide four protocolised evidence-based interventions using custom-designed decision-support algorithms. Patients with specific contraindications to corticosteroid therapy or early mobilisation will not receive these interventions. The four interventions are as follows.

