#### Control group

During the non-interventional control periods (as determined by the stepped-wedge rollout schedule), patients admitted with community-acquired pneumonia under eligible general internal medicine units will receive usual care at the discretion of the treating general internal medicine multidisciplinary team. Ultimate responsibility for treatment decisions is generally made by a supervising general internal medicine consultant physician, who reviews patients on the morning after admission and on supervisory ward rounds conducted three times per week. Junior medical staff (registrar level) are also involved in day-to-day medical decision-making but allied health practitioners (physiotherapists and dieticians) are generally only involved if there has been a formal referral process initiated by a member of the treating medical or nursing team.

Pre-trial standard care at the study institution (auditing conducted in 2015) consisted of the following proportions of patients with community-acquired pneumonia receiving: corticosteroids (43%), a guideline-compliant antibiotic (65%) and physiotherapy (including early mobilisation) (63%; median time to initiation, two days). No parenteral antibiotic stopping rules are in place (median duration 3 days), while malnutrition risk screening in inpatients across all health-service patients is 72%.

All other aspects of patient care, including fluid delivery, use of lines and drains, general nursing care and discharge planning, will be provided at the discretion of the general internal medicine teams, as per routine institutional practice or protocols.

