### Secondary trial outcome measures

Secondary outcome measures comprise routinely collected institutional data and include:Inpatient mortality30 day and 90 day readmission rates and mortalityAdmission to the intensive care unit from inpatient wards and requirement for and duration of mechanical ventilationTotal individual per-separation hospital clinical costing, as determined by the institutional dedicated clinical costing unit using the Power Performance Manager™ software platform (Power Health Solutions, Adelaide, Australia)Protocol adherence (proportion of evidence-based treatments delivered in each group; proportion of patients receiving the whole bundle; reasons for protocol adherence failure)Serious adverse events (including the incidence of in-hospital hyperglycaemia requiring new insulin prescription, adverse drug reactions where it is required that the drug use is stopped, falls or clinical deterioration requiring urgent medical review during early mobilisation), other adverse events and clinical complications (Table 2) occurring prior to admission, during inpatient stay or requiring re-presentation to hospital within 30 days.

**Table 2 Tab2:** Reporting of serious adverse events, adverse events and complications

Complication group	Complication
Pneumonia-associated complications	Respiratory failure requiring intubation
	Hypotension requiring vasopressors
	Empyema *Defined as: documented in registrar admission assessment, radiologist chest X-ray report or medical discharge summary*
	Acute respiratory distress syndrome *Defined as: documented in registrar admission assessment, radiologist chest X-ray report or medical discharge summary*
	Pleural effusion *Defined as: diagnosed on radiologist chest X-ray report*
	Increased confusion from baseline
Other adverse events	Death from any cause
	Fall with fracture
	Cardiac decompensation *Defined as: documented in registrar admission assessment, radiologist chest X-ray report or medical discharge summary*
	Cardiac event *Defined as: diagnosed episode of cardiac ischaemia or new cardiac arrhythmia*
	Acute stroke *Defined as: documented in registrar admission assessment, radiologist report or medical discharge summary*
	Thromboembolic event *Defined as: pulmonary embolus or deep vein thrombosis documented in registrar admission assessment, radiologist report or medical discharge summary*
	Confirmed or suspected gastrointestinal bleeding

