Adverse events in patients receiving corticosteroids	Adverse drug reaction where it is required that the drug is stopped (percentage of total number receiving burst corticosteroid dose)
	In-hospital hyperglycaemia requiring new insulin prescription (percentage of known diabetics)
Adverse events compatible with antibiotic use	Adverse drug reaction, where it is required that the drug use is stopped
Adverse events in patients receiving early mobilisation	Falls during physiotherapy (percentage of total physiotherapy sessions delivered)
	Clinical deterioration during physiotherapy requiring urgent medical review (percentage of total physiotherapy sessions delivered) (see Additional file 2)
	Mobilisation ceased owing to sustained observations outside target range (percentage of total physiotherapy sessions delivered) (see Additional file 2)

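### Apart from falls with fracture, falls count only during physiotherapy sessions, so the plan cannot show whether the service changes non-fracture falls among enrolled patients

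*Protocol article*

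**What the plan says.** The section on secondary trial outcome measures makes serious adverse events a secondary outcome and includes "falls or clinical deterioration requiring urgent medical review during early mobilisation". Read alone, that phrase leaves it unclear whether falls are limited to mobilisation. The abstract settles it by naming as the serious adverse events "rates of hyperglycaemia requiring new insulin; falls during mobilisation".

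Table 2 then gives two falls items. "Fall with fracture" is listed under other adverse events and applies to every patient. The second, "Falls during physiotherapy (percentage of total physiotherapy sessions delivered", comes under the heading "Adverse events in patients receiving early mobilisation". The Data monitoring section also ties its example of a reportable fall to physiotherapy, and there requires an injury.

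On exposure to sessions, the Control group section reports from a 2015 audit "physiotherapy (including early mobilisation) (63%; median time to initiation, two days", and says that allied health staff generally become involved only after a formal referral. Table 1, Item 11 expects this to continue in usual care ("Anticipate existing data on proportions to be maintained"). For the service it says "Aim for relevant proportions to exceed 70% for interventions (i) and (ii), and 85% for (iii) and (iv", where (iii) is early mobilisation. The service's sessions are daily and start within 24 hours. The Statistical methods section analyses primary and secondary outcomes as randomised.

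**The concern.** Early mobilisation is one of the four components, in a population whose average age is given as 75 years under Trial setting. Its effect on falls could go either way. A patient mobilised early may later walk unsupervised and fall, or better conditioning may prevent falls. Both effects would show mainly outside sessions, where only a fall with fracture is counted.

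The per-session row cannot stand in for this. A patient with no session adds nothing to its numerator or denominator. Those who do contribute are, under usual care, a subset chosen by referral and, under the service, nearly everyone by design. The row therefore compares groups formed after allocation, by the very thing the intervention alters. A favourable or neutral result could be read as saying that the service does not affect falls, which it would not have tested.

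**Working it through.** The protocol derives no figure on this point, so there is nothing to reproduce beyond the complement of the audit figure.

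**Who can contribute under usual care.** 1 − 0.63 = 0.37. On the audit figure, 37% of usual-care patients have no physiotherapy and cannot enter the row.

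**What the row responds to.** For one group let *c* be the share of patients with any session, *s* the sessions per such patient, *r* the falls per session and *o* the off-session falls per enrolled patient.

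- Planned row = (*c* × *s* × *r*) / (*c* × *s*) = *r*
- All falls per enrolled patient = *o* + *c* × *s* × *r*

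The term *o* does not appear in the planned row, so no value of *o* can move it.

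**Illustration.** From the protocol: *c* = 0.63 for usual care, *c* = 0.85 for the service (the target), and 640 patients. Assumed: an even split of 320 per condition, *s* = 2 and 4, *r* = 0.2% in both groups, and *o* = 4% under usual care.

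- Sessions: 320 × 0.63 × 2 = 403 and 320 × 0.85 × 4 = 1,088
- Falls in sessions: 403 × 0.002 = 0.81 and 1,088 × 0.002 = 2.18
- In-session falls per 100 enrolled: 0.63 × 2 × 0.2 = 0.25 and 0.85 × 4 × 0.2 = 0.68

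| Off-session falls under the service (assumed) | Planned row, usual care vs service | All falls per 100 enrolled, usual care vs service |
|---|---|---|
| 2% | 0.2% vs 0.2% | 4.25 vs 2.68 |
| 4% | 0.2% vs 0.2% | 4.25 vs 4.68 |
| 8% | 0.2% vs 0.2% | 4.25 vs 8.68 |

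With *r* = 0.5% the row reads 0.5% vs 0.5% throughout, and all falls are 4.63 vs 3.70, 5.70 or 9.70. The planned row is the same whether total falls drop, stay similar or double.

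**Does the fracture item fill the gap?** The protocol gives no fracture-fall risk. Assuming 0.1% to 0.5%, 640 patients give 640 × 0.001 = 0.64 to 640 × 0.005 = 3.2 events. A simple two-proportion comparison with 320 per condition has about 5% to 11% power to detect a doubling. It is too rare an event to answer the question.

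**The case against.** The row is a component safety measure and is coherent as one. Its table heading limits it to recipients, as the corticosteroid group of Table 2 does with its own denominators. Nothing in the protocol says the row is meant to show the service's effect on falls overall. That stands, and is why the row should be kept. It does not remove the gap, because these falls are named within a secondary outcome to be analysed as randomised and no other item records non-fracture falls.

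A reader might infer that the service will look worse simply because it gives more sessions, for example by a ratio of 0.85/0.63 = 1.35 at equal risk. The protocol does not support this. That ratio needs a count per enrolled patient, whereas the planned measure is per session; at equal per-session risk its ratio is 1.00.

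A reader might also infer that the plan says nothing about falls outside sessions. That is too strong: falls with fracture are counted in everyone, and the list of reportable serious events under Data monitoring is expressly open-ended. But a report to the ethics committee is not a defined outcome.

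Nor should 37% be set against 15% as a measured contrast. The first comes from a pre-trial audit of any physiotherapy, not stated to be limited to the general internal medicine units. The second is the complement of an adherence target for early mobilisation, and the protocol does not say whether patients with contraindications count towards that target. The figures show the direction of the difference in exposure, not its size in the trial.

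Finally, an all-falls count has its own weaknesses. Service patients are seen daily by an unblinded team, so minor falls may be charted more fully. Power is limited: with 320 per condition and a simple two-proportion test, about 57% for 4% vs 8% and about 32% for 4% vs 2%, before any loss from the stepped-wedge design. Both points stand as cautions on interpretation.

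**Conclusion.** The point holds for non-fracture falls. As defined, the plan can describe how safe the delivered sessions are. It cannot show whether the service changes non-fracture falls among enrolled patients, because falls between sessions, and falls in patients with no session, are not events.

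The structural part rests on the protocol's wording alone: off-session falls do not enter the row, and session receipt follows allocation. The numerical illustration rests on assumed session counts, per-session risk and off-session fall rates, none of which the protocol gives. No direction of bias in the planned row is claimed. The primary outcome and the sample size are untouched; what is affected is one of the two harms that the abstract singles out.

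**What to change.** In the secondary outcome list and Table 2, add a harm defined as any inpatient fall from enrolment to discharge, with or without fracture, in or out of a physiotherapy session. Take it from the medical record for every enrolled patient and compare it per enrolled patient, or per patient-day, in both groups with the model for secondary outcomes. Keep falls per physiotherapy session as a descriptive session-safety figure, and say that it is not a between-group comparison of the service's effect on falls. Keep the fracture item as it is.

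The cost is small. The section on daily clinical monitoring already has adverse events taken from the medical record for all enrolled patients, so this adds one field and slightly more abstraction. When the result is reported, acknowledge the limited power and the possibility of fuller detection of minor falls in service patients.

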### Protocol adherence

Protocol adherence to each component of the intervention will be measured and reported as follows.

### Intervention 1 – Corticosteroids

Prescription of 50 mg prednisolone daily (or equivalent dose of hydrocortisone or other corticosteroid) within 36 hours of arrival at the emergency departmentMinimum 7 day duration of corticosteroid prescription

### Intervention 2 – Early switch to oral antibiotics

Adherence to intravenous antibiotic stopping rules, where the switch to oral therapy is made within 24 hours of the patient meeting the criteria for clinical improvement

### Intervention 3: Early mobilisation

Completion of first session of early mobilisation with a physiotherapist within first 24 hours of admission to a general internal medicine unit, and achieved minimum physical activity of sitting out of bed > 20 minutesOn > 70% of eligible admission days (early mobilisation not contraindicated) progressive movement is achieved in a physiotherapy sessionPatient movement either upright in bed or to the commode for toileting alone will be considered insufficient [16]

### Intervention 4: Malnutrition risk screening and targeted nutrition therapy

Adherence will be measured by:Calculation of Malnutrition Screening Tool score within 24 hours of admission to a general internal medicine unitImplementation of appropriate nutrition therapy in response to Malnutrition Screening Tool score (none, high-energy high-protein diet or dietician referral and review within 24 hours)

### Data collection (see Fig. 4)

#### At enrolment (baseline measures)

Demographic and clinical characteristics will be recorded by collection of the following variables (directly from the patient or the medical record): site, patient age and sex, admitting medical unit, eligibility criteria (age, chest X-ray findings, cough, dyspnoea, temperature, chest auscultation findings, peripheral blood leucocyte count), vital signs on admission (temperature, heart rate, blood pressure, respiratory rate, pulse rate, confusion), estimated glomerular filtration rate, residential care status (independent living, supported accommodation, aged care facility), pre-morbid mobility, function and exercise tolerance, CORB score (derived from confusion, oxygenation, respiratory rate and blood pressure), any relevant comorbidities (e.g. diabetes, immunosuppression, adrenal insufficiency, chronic obstructive pulmonary disease, chronic cardiac failure, malignant process), number of routine medications used by the patient, baseline corticosteroid dose (if any), baseline insulin usage, relevant drug allergies, enrolment in a concurrent inpatient research trial, any decision to initiate palliative care on admission, any adverse events or complications that occur prior to enrolment.

#### Daily during admission (clinical monitoring)

Circumstances necessitating withdrawal of a participant from the study after enrolment but within 48 hours of admission to a general internal medicine unit will be recorded.

The following variables will be collected from the medical record and reported for all enrolled patients: any serious adverse events, adverse events or clinical complications (see Table 2), any decision to palliate, adherence to protocol for Interventions 1 to 4 (as listed previously).

Daily vital signs (SpO_2_, supplementary oxygen requirements, heart rate, respiratory rate, blood pressure, temperature) will be measured every 4 hours as per routine clinical care and used to ascertain the switch to oral from intravenous antibiotics.

Blood glucose readings as clinically indicated and requested by treating team, and oral intake status (ability to tolerate oral medications and absence of gastrointestinal problems that may affect drug absorption) will also be reviewed daily.

#### At discharge (clinical and outcome measures)

On acute hospital discharge via review of the medical record, the admission chest X-ray report (as reported by the radiologist), along with other diagnostic test results (respiratory PCR, legionella urinary antigen, sputum and blood cultures, serology) will be recorded.

The following variables will be extracted directly from the institutional data warehouse and linked to the study dataset by unique identifier (admission episode number): age, sex, marital status, language status, primary ICD-10 discharge code and allocated diagnosis-related group, ICD-10 co-morbidity groupings used in the Charlson’s Co-morbidity Index (derived using an existing algorithm that interrogates ICD-10 coding data), intensive care unit length of stay and duration of mechanical ventilation, total length of stay measured in days (to three decimal places) and broken down to emergency department, inpatient ward, rehabilitation or sub-acute care and hospital in the home), inpatient mortality and total individual clinical costings.

#### At 30 and 90 days following presentation to the emergency department (outcome measures)

Mortality, institutional readmission within 30 and 90 days and total institutional costs incurred at 30 and 90 days will also be extracted from the institutional data warehouse and linked to the study dataset as described previously.

Any adverse event or complication (as defined in Table 2) that requires re-presentation to hospital noted in the electronic medical record within 30 days of initial arrival in the emergency department will be recorded.

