At the time this trial was designed, a body of evidence had accrued to support the efficacy of adjunct corticosteroids, including results from two large randomised controlled trials (RCTs) showing that they (1) reduced treatment failure in severe community-acquired pneumonia [11] and (2) shortened time to clinical stability and time to effective hospital discharge without an increase in adverse complications [12]. Although there is a slightly higher risk of hyperglycaemia, this can be effectively treated with insulin with no long-term effects [12, 13]. Meta-analyses had also confirmed these findings and demonstrated an overall lower rate of complications in corticosteroid-treated patients, including a reduction in the need for vasopressors or mechanical ventilation in patients with community-acquired pneumonia routinely prescribed corticosteroids [14, 15]. Early mobilisation safely and effectively reduces length of stay [16], as does an early switch from intravenous to oral antibiotics [17]. A recent randomised trial of both these interventions found that length of stay was shortened by two days compared with standard care [18]. In a recent meta-analysis of malnourished medical inpatients (including those admitted with community-acquired pneumonia), systematic screening for malnutrition risk and targeted nutritional therapy reduced non-elective readmission rates [19].

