### Primary outcome measure

The primary outcome measure will be hospital length of stay, calculated from arrival in the emergency department until discharge from the health service, based on date and time (note that data will be collected in minutes but converted to days). This information is routinely collected at the institution for all inpatients.

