## Discussion

IMPROVE-GAP will be the first RCT powered and designed to investigate a service-delivery approach to improving the translation of evidence into clinical practice in community-acquired pneumonia, one of the highest-burden conditions affecting health systems worldwide. Its stepped-wedge design is better suited than other RCT approaches to evaluating a health-service intervention in a ‘real-world’ operational context. It also has pragmatic advantages in that once the study is completed, the intervention has effectively been implemented in the health system in which it has been tested and, should the implementation be found to be financially and clinically effective, can then be continued indefinitely. It may therefore demonstrate the power of stepped-wedge trial designs to accelerate the ‘time to translation’ when implementing clinical trial evidence in routine clinical practice [21]. This has value both to patients, who benefit from improved outcomes and, if the intervention also has an efficiency dividend, to the health system. We acknowledge the possibility that, despite considering patients masked to allocation owing to the waiver of consent, that it is possible that some patients were aware of study interventions. However, we feel that the risk of selection bias was minimised, as allocation to treating unit was determined by established practice according to day of admission or previous admitting unit. Our design also aimed to minimise attrition bias (by using routinely available outcome measures, such as length of stay, clinical cost and inpatient mortality) although readmission rate may be susceptible to attrition bias, as readmission to other health services was not routinely available nor collected.

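### Readmission and re-presentation are timed from emergency presentation, so time at risk is the window minus length of stay, and a shorter stay alone raises the count

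*Protocol article*

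**What the plan says.** All references are to the protocol article.

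- **Follow-up data collection.** The section is headed "At 30 and 90 days following presentation to the emergency department". The items it lists are "Mortality, institutional readmission within 30 and 90 days and total institutional costs incurred at 30 and 90 days". The only source it names for them is the institution's own data warehouse. The same section records complications that require re-presentation within 30 days, counted from initial arrival in the emergency department.
- **Primary outcome measure.** Length of stay is "calculated from arrival in the emergency department until discharge from the health service".
- **Data collection at discharge.** Total stay is "broken down to emergency department, inpatient ward, rehabilitation or sub-acute care and hospital in the home", so sub-acute care and home-based hospital care belong to the index stay.
- **Secondary trial outcome measures.** Readmission and mortality at 30 and 90 days are listed without a time origin. The data-collection section is the place that supplies one.
- **Economic analysis.** Costs, including any readmission, run over the 90 days after discharge. Mortality for the cost-effectiveness analysis runs to 90 days from the original admission.
- **Discussion.** It concedes that "readmission rate may be susceptible to attrition bias, as readmission to other health services was not routinely available nor collected". The time origin is not mentioned.

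**The concern.** Readmission is where a reader will look to see whether earlier discharge led to more returns to hospital. With the clock started at arrival, days spent in the index stay use up the window. A stay longer than 30 days cannot have a 30-day readmission at all. The quantity that determines exposure is the one the intervention is meant to change, so success on the primary outcome pushes readmission up even if patients are no more likely to return on any given day after discharge. Complications requiring re-presentation share the same clock.

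There is also an internal mismatch. A readmission on day 92 from presentation after a 5-day stay falls on day 87 after discharge. It would enter the economic costing but not the 90-day readmission outcome, so the cost and clinical results would count different events.

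**Working it through.** The plan states no figure for this point, so there is nothing to reproduce. The check is how far the window alone moves the outcome.

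**Inputs from the protocol article**
- Windows W of 30 and 90 days from presentation.
- Length of stay L from the same origin.
- Reduction in stay of 2 days, taken as an illustration from the trial cited in the Background, which "found that length of stay was shortened by two days compared with standard care".

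**Assumptions (not in the document)**
- Control stay L of 6, 8 or 10 days, treated as one value for all patients.
- Readmission risk R over the 30 days after discharge of 10, 15 or 20%, identical in both phases.
- Daily risk either constant or front-loaded (Weibull, shape 0.7).

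**Step 1. Time at risk.** Time at risk = W − L.
- At 30 days, with L = 8 falling to 6: 22 days becomes 24, a 9.1% gain. For L of 6 to 10 days the gain is 8.3 to 10%.
- At 90 days, with L = 8 falling to 6: 82 days becomes 84, a 2.4% gain.

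**Step 2. Readmission with constant daily risk.** h = −ln(1 − R)/30 and P = 1 − exp(−h(W − L)).
- R = 15%, h = 0.00542, 30 days: 11.2% (L = 8) against 12.2% (L = 6). Odds ratio = (0.1219/0.8781)/(0.1124/0.8876) = 1.10.
- R = 20%, h = 0.00744, 30 days: 15.1% against 16.4%, odds ratio 1.10.
- R = 15%, 90 days: 35.9% against 36.6%, odds ratio 1.03.
- Over all nine combinations, the 30-day rise is 0.6 to 1.3 points (odds ratio 1.09 to 1.11). The 90-day rise is 0.5 to 0.8 points (odds ratio about 1.03).

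**Step 3. Front-loaded risk.** P = 1 − exp(−((W − L)/s)^0.7), with s = 30/(−ln(1 − R))^(1/0.7).
- R = 15%, 30 days: 12.3% (L = 8) against 13.0% (L = 6), a rise of 0.7 points.
- Over all nine combinations, the 30-day rise is 0.5 to 1.0 points (odds ratio about 1.06 to 1.08). It is smaller because the days added fall late, when risk is lower.

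**Step 4. After the change.** Counted from index discharge, every patient discharged alive has a window of exactly 30 or 90 days. The difference due to window length is zero whatever the stay.

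**Step 5. Mortality.** A death can occur on any day from presentation, in or out of hospital, so a window fixed from presentation does not shrink or grow with stay. Dependence enters only if deaths after discharge are partly unseen. With true mortality M by day 30 and capture share c of post-discharge deaths, observed mortality = D(L) + c(M − D(L)). Here D(L) = 1 − exp(−kL) is the probability of dying during the stay, with k = −ln(1 − M)/30. For M of 8 to 13% (assumed, the upper value borrowed from the Background) and a 2-day shorter stay, observed mortality falls by 0.5 to 0.9 points at c = 0, by 0.3 to 0.5 points at c = 0.5, and by 0 at c = 1. The document gives no value for c.

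**The case against.** **A fixed window from presentation is a defensible choice.** It gives every enrolled patient one common clock, whereas counting from discharge restricts the analysis to patients discharged alive, which happens after randomisation and could be affected by the intervention. This is fair but carries limited weight: only discharged patients can be readmitted under either clock. Keeping the presentation-based version as a sensitivity analysis meets it.

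**The effect is small beside the precision of the trial.** Taking 320 against 320 patients, and ignoring clustering and period adjustment, the standard error of the difference is √(0.112 × 0.888/320 + 0.122 × 0.878/320) = 2.5 points at the lower pair of rates and 2.9 at the higher pair. A shift of 1.0 to 1.3 points is under half a standard error. The bias also works against the intervention, so it cannot create a false benefit. This stands and limits the weight of the point. It does not remove it, because the bias is systematic, its direction is known, and it can be avoided.

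**The origin appears in a data-collection heading, not in the outcome definition.** True, but that section is the one that supplies an origin, and it repeats it for re-presentations. The different clock under Economic analysis makes a single definition more necessary.

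**A stronger reading does not hold.** A reader might infer that 30- and 90-day mortality also depends mechanically on length of stay, or that deaths after discharge are certainly under-counted. The article does not support this. Presentation is a sound origin for death. Mortality comes from the data warehouse, but nothing says what feeds the warehouse or that outside deaths are absent from it. The admission that "readmission to other health services was not routinely available nor collected" concerns readmission. Any count of missed deaths would rest on assumed inputs and would be a total shortfall, not a difference between phases.

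**Conclusion.** The point holds for readmission and for complications requiring re-presentation. Their time at risk is the window minus the primary outcome, which follows from the protocol's own definitions, and the direction needs no assumption beyond a shorter stay. The size does rest on assumptions: about 0.5 to 1.3 percentage points at 30 days for a 2-day reduction, with an odds ratio near 1.10 under constant daily risk and somewhat less if risk is front-loaded, and about 1.03 at 90 days. The bias is modest, runs against the intervention and leaves the primary outcome untouched.

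The difference between the follow-up section and the Economic analysis section is a separate inconsistency that needs resolving whatever view is taken of the bias.

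For mortality there is no defect in the time origin, only an open question about capture of deaths outside the institution.

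**What to change.** 1. Define 30- and 90-day readmission, and re-presentation with a complication within 30 days, from index discharge among patients discharged alive. Time from discharge with death as a competing event would serve equally well.
2. Keep the presentation-based version as a sensitivity analysis.
3. Reconcile the follow-up section with the Economic analysis section, so that readmissions and their costs are counted over the same period.
4. Leave mortality anchored at presentation. State whether the data warehouse captures deaths outside the institution. If it does not, label the outcome as deaths recorded by the health service and qualify the cost-effectiveness result accordingly.

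The cost is low. Discharge date and time are already collected for the primary outcome, so no new variable is needed. Follow-up extraction ends later by the length of the index stay, and the main readmission analysis conditions on discharge alive, which the sensitivity analysis addresses. The mortality item needs only a sentence of clarification or a change of label.
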